# Scaling and sustaining COVID-19 vaccination through meaningful community engagement and care coordination for underserved communities: hybrid type 3 effectiveness-implementation sequential multiple assignment randomized trial

**DOI:** 10.1186/s13012-023-01283-2

**Published:** 2023-07-14

**Keywords:** Implementation science, Hybrid type 3 effectiveness-implementation study, Sequential multiple assignment randomized trial, COVID-19, Underserved communities, Health equity, Care coordination, mHealth, Vaccination

## Abstract

**Background:**

COVID-19 inequities are abundant in low-income communities of color. Addressing COVID-19 vaccine hesitancy to promote equitable and sustained vaccination for underserved communities requires a multi-level, scalable, and sustainable approach. It is also essential that efforts acknowledge the broader healthcare needs of these communities including engagement in preventive services.

**Methods:**

This is a hybrid type 3 effectiveness-implementation study that will include a multi-level, longitudinal, mixed-methods data collection approach designed to assess the sustained impact of a co-created multicomponent strategy relying on bidirectional learning, shared decision-making, and expertise by all team members. The study capitalizes on a combination of implementation strategies including mHealth outreach with culturally appropriate messaging, care coordination to increase engagement in high priority preventive services, and the co-design of these strategies using community advisory boards led by Community Weavers. Community Weavers are individuals with lived experience as members of an underserved community serving as cultural brokers between communities, public health systems, and researchers to co-create community-driven, culturally sensitive public health solutions. The study will use an adaptive implementation approach operationalized in a sequential multiple assignment randomized trial design of 300 participants from three sites in a Federally Qualified Health Center in Southern California. This design will allow examining the impact of various implementation strategy components and deliver more intensive support to those who benefit from it most. The primary effectiveness outcomes are COVID-19 vaccine completion, engagement in preventive services, and vaccine confidence. The primary implementation outcomes are reach, adoption, implementation, and maintenance of the multicomponent strategy over a 12-month follow-up period. Mixed-effects logistic regression models will be used to examine program impacts and will be triangulated with qualitative data from participants and implementers.

**Discussion:**

This study capitalizes on community engagement, implementation science, health equity and communication, infectious disease, and public health perspectives to co-create a multicomponent strategy to promote the uptake of COVID-19 vaccination and preventive services for underserved communities in San Diego. The study design emphasizes broad engagement of our community and clinic partners leading to culturally sensitive and acceptable strategies to produce lasting and sustainable increases in vaccine equity and preventive services engagement.

**Trial registration:**

ClinicalTrials.gov Identifier: NCT05841810 May 3, 2023

Contributions to the literature
This study applies a sequential multiple assignment randomized trial design to understand and accelerate the impact of a co-created health prevention program designed to address COVID-19 vaccine equity and primary care engagement for communities of color served in a Federally Qualified Health Center.This study integrates methods from community engagement, implementation science, health equity, health communication, infectious disease, and public health perspectives to mitigate health disparities and advance health equity.This study focuses on the rarely examined implementation outcome of sustained engagement in preventive services among historically underserved communities.

## Background

### COVID-19 disparities experienced by underserved communities in California

The COVID-19 pandemic has punctuated pervasive health disparities among immigrant, refugee, Latino, Asian, and Black, Indigenous, People of Color (BIPOC) communities [1, 2]. These communities are significantly more likely to experience mortality and morbidity from COVID-19, along with lagging testing and vaccination rates compared to predominantly white communities [3]. Despite the availability of multiple safe and effective vaccines that have been recommended by the Centers for Disease Control and Prevention (CDC), vaccination rates have been slower and variable in BIPOC communities [4, 5].

Although current data on vaccination rates in the United States of America (USA) offer hope towards ending the COVID-19 pandemic (as of this writing), 85% of adults completed the primary vaccine series; 65% of eligible adults have received a booster dose in addition to completing the primary series; and vaccine uptake has lagged across BIPOC communities in San Diego County with only 51% of Black, 69% of Hispanic, and 71% of Asian residents having completed the primary vaccines series [6]. To address persistent inequities, the CDC National Forum on COVID-19 vaccine emphasizes that “barriers to vaccine access must be removed and evidence-based approaches to improving vaccine confidence and acceptance are essential” [7, 8].

### Multi-level factors driving vaccine hesitancy and vaccine uptake: individual, structural, systemic, and technological

“Vaccine uptake” is defined as the completion of a vaccination series per administration schedule as recommended by medical experts and appropriate institutions. Vaccine uptake is complex and driven by individual-level factors, structural and systemic factors, and technological factors; these impacts are amplified for underserved communities. Although vaccine uptake has increased, underserved communities have been historically overlooked by public health strategies tailored to resource-rich communities with predominantly English-speaking residents [9].

At the individual level, the research and popular literature have increasingly focused on the concept of “vaccine hesitancy.” Vaccine hesitancy refers to delay in acceptance or refusal of vaccination despite availability of vaccination services [10]. Vaccine hesitancy is the midpoint in decision-making between vaccine refusal and acceptance and can be influenced by societal/community norms, individual attitudes (e.g., complacency, confidence), and structural factors (e.g., convenience, access) [11]. A related term, “vaccine confidence,” is defined as the belief that vaccines work, are safe, and are part of a trustworthy medical system [12]. Factors driving vaccine hesitancy and confidence include medical distrust shaped by historical trauma rooted in biomedical research and continues to be reinforced by current experiences of discrimination within medical encounters. The COVID-19 pandemic has also prompted a deluge of information, opinion, and conspiracies known as the “infodemic” which has played a significant role in vaccine hesitancy [13]. Rapid and widespread sharing of both evidence-based and inaccurate information about COVID-19 and vaccines leads some people to inaction. This has been particularly salient in Spanish-language social media [14–17]. Vaccine hesitancy or confidence at the individual level is one, but often not the most, important explanatory variable of vaccine uptake [13]. Additional factors driving uptake are largely related to access, including structural and systemic barriers.

The pandemic has created an overall reduction in timeliness of immunizations and preventive service completion [18, 19] and underscored an urgent need to overcome structural barriers preventing certain populations from accessing high quality, convenient, and affordable healthcare. “Preventive services” are defined as routine, guideline-concordant health care that includes chronic health screenings, check-ups, and patient counseling to prevent illnesses, disease, or other health problems [20]. Vaccine distribution is traditionally embedded within existing healthcare infrastructure that is inequitably designed and inadequately funded. Even among those with a healthcare provider, studies show that BIPOC tend to receive lower-quality healthcare than white people after controlling for insurance status, income, age, and condition severity [21]. As a vaccine comparison, influenza vaccination rates are consistently lower among Black, Latino, and Asian American persons, as well as individuals of lower socioeconomic status (SES), compared with their white and higher SES counterparts [22]. San Diego residents that are particularly impacted by barriers to healthcare access include undocumented residents, isolated community members, individuals whose preferred language is not English, or those who need transportation and access accommodations.

Systemic and logistical factors also impact access to the COVID-19 vaccine. The digital divide (i.e., differential access to technology needed to schedule appointments and obtain updated health information) precludes a sizeable portion of the population from accessing web-based scheduling portals to set up vaccination appointments. Individuals also need to access information in their preferred languages to make informed decisions about vaccination and to schedule vaccination appointments. Compounding these structural factors, concerns about the need to take sick or unpaid leave, or secure childcare, due to vaccine side effects might negatively impact vaccine uptake.

### Promise of implementation science in addressing vaccine hesitancy and uptake for underserved communities

Addressing COVID-19 vaccine hesitancy to promote equitable and sustained vaccination for underserved communities requires a multi-level, scalable, and sustainable approach. It is also essential that efforts acknowledge the broader healthcare needs of underserved communities including engagement in preventive services [23–25]. The current study builds on the project team’s community-engaged infrastructure to conduct a hybrid type 3 effectiveness-implementation trial [26, 27] to examine the impact of a co-created multicomponent implementation strategy on increased and sustained COVID-19 vaccination and engagement in preventive services for underserved communities within a FQHC network. This work will combine methods from implementation science, health equity research, and community engagement.

### Implementation strategies

This study is a hybrid type 3 effectiveness-implementation trial in which the evidence-based interventions are COVID-19 vaccines and age- and gender-specific recommended preventive care services. The three implementation strategies that support the uptake of these evidence-based interventions are as follows: (1) co-creation with community advisory boards (CABs) led by Community Weavers, (2) the use of mobile health (mHealth) technologies for health communication, and (3) care coordination. The next section provides a brief overview of each implementation strategy.

#### Co-creation with CABs led by Community Weavers

Meaningful community engagement is an important factor in facilitating the uptake, implementation, and sustained use of interventions designed to address health inequities [28, 29]. Community engagement, however, is not a trivial task, especially when working with communities representing diverse cultural heritages and languages and whose voices have historically been silenced [30, 31]. In the creation of community-vetted solutions to inequitable vaccine distribution and uptake, as well as access to preventive services, it is critical to utilize approaches that acknowledge and address these historical patterns [32]. *Community Weavers are individuals with lived experience as a member of an underserved community who serve as cultural brokers between communities, public health systems, and researchers to co-create community-driven, culturally sensitive public health solutions* [33, 34]. Community Weavers can bridge the gap between the underserved community and the mainstream public health systems and support research and clinical partners in learning about the priorities, preferences, needs, and strengths of the community, which can lead to solutions that are culturally sensitive and responsive [34]. They can also support the engagement of community members in health care, including COVID-19 vaccination and other preventive services. The Global Action Research Center (ARC), a nonprofit social change organization with expertise conducting participatory action research to address public health needs and a trusted resource for many of the grassroots organizations, will be the key lead in identifying, training, and engaging our Community Weavers in this project. A key component in this process is to engage in co-creation of solutions with members of the community. *Co-creation*builds on the concepts of bidirectional learning and shared decision-making and relies on the expertise brought by all members of the team [35, 36]. Co-creation has been successfully used in diverse contexts, and programs that incorporate co-creation tend to have better uptake, more comprehensive implementation, and lead to more sustained positive outcomes [37–39]. Co-creation has been at the heart of our prior community-engaged COVID-19 research with our community and clinical partners to meaningfully engage diverse community members in participatory methods.

#### Use of mobile health (mHealth) technologies for health communication

Lessons addressing challenges with vaccine distribution and vaccine hesitancy can be drawn from decades of vaccine campaign research from low- or middle-income countries (LMICs) through reverse innovation. Reverse innovation involves replicating an innovation that was originally developed for use in LMIC settings and translating to a high-income country [40]. Traditionally in clinical research, innovation is scaled from high-resource settings to low-resource settings, resulting in predictable challenges with resource limitations impacting feasibility. Reverse innovation allows researchers to derive insights from LMIC implementation research and innovatively adapt for higher-income settings. Given the importance of trust in promoting vaccine uptake, the current study will amplify the voices of trusted local leaders within historically disadvantaged communities. Emerging research illustrates the popularity of mHealth interventions to extend service capacity and reach, promote healthcare engagement, reduce stigma, and promote vaccine acceptance [41]. The use of digital health products has significantly increased during the COVID-19 pandemic era [42]. Important considerations for the implementation of mHealth in real-world settings include technology literacy, personalization of interventions, and perceptions of health risk and status [43]. We will address these considerations to inform the appropriate selection of implementation strategies tailored for context and implementation phase [44].

#### Care coordination

In addition to information on vaccine effectiveness and access through mHealth strategies, additional support with more intense coordination might be needed for some community members. Care coordination is an evidence-based practice that is widely recognized as a core component of high-quality care [45]. It is also a pillar of the patient-centered medical home (PCMH), which is a model of primary care increasingly adopted by healthcare systems, including FQHCs, to meet the needs of diverse patients and to improve experiences, outcomes, safety, and system efficiency for patients, providers, and staff members [46, 47]. We define care coordination as “the deliberate organization of patient care activities between two or more participants involved in a patient’s care to facilitate the appropriate delivery of health care services” [48–50]. Through personalized health education and care management and collaborative problem-solving, care coordinators will work with patients to develop and achieve a health action plan in collaboration with their primary care physician. The National Committee for Quality Assurance (NCQA) leads the most widely adopted evaluation program for PCMH accreditation, called the NCQA Recognition program [51]. Our FQHC healthcare partner has successfully obtained and maintained NCQA recognition, due, in part, to their care coordination program. This study will expand eligibility for care coordination to target reduction of outstanding preventive services, including but not limited to diabetes and cancer screenings, and influenza vaccination, and offer co-created enhancements to maximize cultural relevance to priority patient communities served by the FQHC.

Taken together, these three implementation strategies — co-creation led by Community Weavers, mHealth, and care coordination — have strong potential to accelerate efforts to sustain COVID-19 vaccination uptake and recommended use of preventive services. Research indicates that social determinants of health, such as low SES, educational level, and access to transportation, along with identifying as members of immigrant, refugee, Latino, and BIPOC communities, reduce one’s likelihood to engage in evidence-based preventive services [52, 53]. As a response to the COVID-19 pandemic, many preventive services were delayed, resulting in more members of underserved communities having overdue preventive service needs [54]. Through a multicomponent health program, COVID-19 vaccination will be coupled with engagement of members of underserved communities in broader preventive services. Engagement in preventive services will be addressed through all components of the program including co-creation of strategies, mHealth outreach, and care coordination. Combining care coordination with culturally relevant, linguistically appropriate, and co-created mHealth health promotion messages offer a powerful approach to both facilitating vaccine equity and preventive services engagement.

### Theory of change and implementation science framework

Our study is guided by a theory of change developed by our team through our National Institutes of Health (NIH)-funded research studies and the practical, robust implementation, and sustainability model (PRISM).

#### Theory of change (ToC)

The multicomponent health program will be informed by an overarching ToC that was developed based on the team’s prior work with two CABs. The goal of the CO-CREATE CAB was to directly inform co-created implementation strategies for a tailored COVID-19 testing program and included 22 members representing community residents, public health researchers, and clinical partners. The goal of the STOP COVID-19 CA CAB was to inform materials and resources needed to support vaccine clinical trial participation and equity initiatives in underserved communities and included 11 community leaders representing ten local grassroots community organizations and two policy partners [23, 24]. ToCs have been broadly used to guide the planning, implementation, and evaluation of public health programs in low-resource settings and provide a comprehensive description of how and why a desired change is expected to happen in a particular context [55, 56]. In these two COVID-19 projects, a rigorous, multistep process was used to create a separate ToC for each CAB [24] which were overlaid to create an overarching, combined ToC. This combined ToC will be confirmed and refined and used to inform our strategy selection and implementation and evaluation planning.

#### Practical, Robust Implementation, and Sustainability Model

The Practical, Robust Implementation, and Sustainability Model (PRISM) will guide the optimization, implementation, and evaluation of our multicomponent health program [57, 58]. PRISM allows for multi-level conceptualization of implementation efforts (context domains) and also provides guidance on how to measure relevant proximal implementation outcomes through integration of the RE-AIM measures (reach, effectiveness, adoption, implementation, maintenance) — one of the most widely used sets of implementation measures [59]. PRISM is ideal for guiding our real-world community-based research project because it accounts for multi-level effects; it builds on several implementation science frameworks and can guide development, implementation, and evaluation. Multiple levels of context will be considered: recipient characteristics (community members and delivery agents — Community Weavers and care coordinators), intervention characteristics (perceived by diverse partners), implementation and sustainability infrastructure within communities and clinics, and the external environment (national guidelines and regulations). These factors will be considered during the co-creation and optimization of the multicomponent health program and assessed dynamically across the lifetime of the study. Several studies show that the reach, adoption, implementation, and sustainment of interventions are related to how well the intervention is integrated into the local context [59–61]. These factors will be assessed in addition to effectiveness, using the reach, effectiveness, adoption, implementation, and maintenance (RE-AIM) framework.

### Aims

The specific aims of the study are as follows:Aim 1: Optimize a multicomponent health program to promote COVID-19 vaccine uptake and engagement in preventive healthcare using our established co-creation approach to address multi-level (individual, community, systemic) barriers to vaccine uptake and preventive services engagement.Aim 2: Evaluate the implementation, effectiveness, and sustainment of the multicomponent COVID-19 vaccine and preventive services engagement program using a hybrid type 3 effectiveness-implementation sequential multiple assignment randomized trial (SMART) design across immigrant, refugee, Latino, and BIPOC communities in Central, North, and East San Diego.

## Methods

### Design

We will optimize, implement, and test the impact of a multicomponent health program that includes three implementation strategies: co-creation led by Community Weavers, mHealth outreach, and care coordination (described earlier). A participatory approach will be used to engage community members in co-creating and optimizing mHealth outreach and care coordination program components (Aim 1). A hybrid type 3 effectiveness-implementation SMART design will assess the impact of the multicomponent health program on implementation and clinical outcome measures (Aim 2) [62, 63]. See Fig. 1 for the study’s conceptual model.

**Fig. 1 Fig1:**
[figure not shown]
Conceptual model

Through the team’s ongoing community-engaged COVID-19 studies and guided by PRISM, determinants that underlie COVID-19 testing and vaccine disparities in underserved communities (immigrant, refugee, BIPOC, and Latino families) were identified. These determinants include unique explanatory models of health and COVID-19 (intervention PRISM domain), structural and systemic challenges to vaccination and preventive services engagement (implementation and sustainability infrastructure PRISM domain), FDA-approved or authorized COVID-19 vaccines available to all adults (external environment PRISM domain), and the varying needs and characteristics of underserved communities located in our target geographic regions (recipients PRISM domain). It is hypothesized that the selected implementation strategies will exert their impact on implementation and clinical outcomes through vaccine confidence and service navigation support (mechanisms). Implementation outcomes are based on RE-AIM and expected to affect our clinical outcomes (effectiveness).

Clinical outcomes are based on the Office of Disease Prevention and Health Promotion’s Healthy People 2020 objectives [64]. A hybrid type 3 design was selected because there is strong evidence for our clinical interventions (highly effective COVID-19 vaccines and evidence-based preventive services) and effectiveness data for the selected implementation strategies delivered individually. The study’s experimental design follows a SMART randomized structure to introduce the more intensive care coordination component only to those who are not responding to usual care or the lower intensity and less-resource intensive mHealth messaging component allowing for more efficient resource allocation. The Community Weaver-led co-creation component will be included in both mHealth and care coordination since this component is at the heart of the meaningful community engagement and the Community Weaver’s role will be critical for both strategies.

The multicomponent strategy is an adaptive approach that utilizes tailored mHealth messaging and care coordination to increase COVID-19 vaccine uptake. The SMART assignment arms are described in Table 2. The trial will span 4 years inclusive of 3 years of active implementation and 1 year of sustainment/maintenance. As outlined in Fig. 2, both randomization and analysis will be conducted at the individual participant level. At enrollment, participants will be stratified by current COVID-19 vaccination status and status of other preventive services vis-à-vis a risk score and then randomized into the first-stage intervention (mHealth outreach or standard of care). Response or lack of response after the completion of the first stage intervention will determine if participants continue in their initial first-stage intervention or re-randomized to increased intensity intervention. Nonresponders in the standard of care arm will be equally re-randomized into either mHealth outreach or care coordination for stage 2. Nonresponders in mHealth outreach will be re-randomized into mHealth or mHealth plus care coordination for stage 2. Nonresponse will be defined as not being up to date on COVID-19 vaccination OR having at least one outstanding preventive service need.

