	COVID-19 vaccine uptake	Up-to-date vaccine record defined as completed vaccine series and required boosters as recommended by Centers for Disease Control guidelines for COVID-19 vaccination at the time of implementation to be confirmed through electronic health records
	Preventive services engagement	Up-to-date age- and gender-specific preventive services (e.g., mammograms, adult immunizations, blood pressure screenings, A1c screenings, colorectal cancer screenings). Standards will be defined for each participant based on their demographic and health characteristics

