### Power calculations

Primary effectiveness outcomes will be COVID-19 vaccine (initial and bivalent booster) completion at a sustained rate of 70% (consistent with Healthy People 2020 influenza vaccination goal for adults aged 18 + years) [70]. Secondary effectiveness outcomes will be an increase in preventive service engagement defined as completing a physical exam and at least one recommended preventive care screening (e.g., mammogram, A1c screening, colorectal cancer screening) annually and increases in vaccine confidence. Data on other recommended adult immunizations (e.g., influenza, shingles) will be extracted from patient electronic health records (EHRs). Primary implementation outcomes will be reach, adoption, implementation, and maintenance up to 2-year post-implementation. Target sample size was determined using methods described by Kidwell et al. [71] for a SMART design with a binary outcome. A power analysis was conducted to inform our targeted sample size based on the following assumptions: (1) probability of success for adaptive health interventions of 0.70; (2) estimated response rate for standard of care of 0.45 (current vaccination rate among target population); and (3) equal re-randomization after first-stage intervention for nonresponders. Allowing for a 5% type-1 error and 80% power, a sample size of at least 252 is needed to evaluate an effect size of 0.25. Assuming a 15% loss to follow-up during the 2-year intervention period, our target enrollment of 300 participants will ensure sufficient sample size for analysis.

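### Stage-1 response is a composite of vaccination and services in the design but the vaccination rate alone in the power section, so stage 2 mixes vaccinated and unvaccinated participants in an unknown proportion

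*Protocol article*

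**What the plan says.** All places are in the protocol article.

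- **Methods, Design (text after Fig. 1), trigger.** "Nonresponse will be defined as not being up to date on COVID-19 vaccination OR having at least one outstanding preventive service need". The decision is taken once stage 1 is over: "Response or lack of response after the completion of the first stage intervention will determine if participants continue in their initial first-stage intervention".
- **Same section, stage-2 options.** "Nonresponders in the standard of care arm will be equally re-randomized into either mHealth outreach or care coordination for stage 2". For the other arm: "Nonresponders in mHealth outreach will be re-randomized into mHealth or mHealth plus care coordination for stage 2".
- **Same section, rationale.** The SMART structure is meant to "introduce the more intensive care coordination component only to those who are not responding to usual care or the lower intensity" mHealth component, so that resources are used efficiently. The stated purpose of the adaptive strategy is COVID-19 vaccine uptake.
- **Power calculations.** COVID-19 vaccine completion is primary. Preventive service engagement is secondary and is met by a physical exam and at least one recommended screening a year. One planning assumption is the "estimated response rate for standard of care of 0.45 (current vaccination rate among target population").
- **Table 4.** The services standard is wider: "Up-to-date age- and gender-specific preventive services (e.g., mammograms, adult immunizations, blood pressure screenings, A1c screenings, colorectal cancer screenings"), set for each participant individually.

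**The concern.** The word response carries two meanings. In the design section it is the joint event of being up to date on vaccination and having no service outstanding. In the power section it is vaccination alone. The joint event cannot be more frequent than either part, so 0.45 is a ceiling for the composite rate and not an estimate of it.

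The trigger is also stricter than the power section's own outcomes. Someone who is vaccinated, has had the physical exam and a mammogram, but is due colorectal screening, has met both the vaccine and the service outcome and is still re-randomised.

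At stake is the stage-2 evidence on vaccination. Each re-randomised group will contain people who already have that outcome. The article gives no expected proportion for them and no step to keep it balanced between groups.

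**Working it through.** **1. The plan's own figure.** Inputs from Power calculations: success 0.70 v 0.45, type-1 error 5% (two-sided assumed), power 80%. The article does not print its formula. A log-odds-ratio calculation gives

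n = (1.960 + 0.842)² × [1/(0.70×0.30) + 1/(0.45×0.55)] / (ln 2.852)² = 62.9.

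The usual SMART multiplier is 2(2 − r), with r the stage-1 response rate.

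- r = 0 (everyone re-randomised): 4 × 62.9 = 251.6, that is 252, the stated figure.
- r = 0.45: 3.1 × 62.9 = 195.
- r = 0.28 or 0.19 (composite rates from step 2): 216 or 228.

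So 252 appears to use 0.45 as the comparator's success rate and to assume no responders. With 15% loss, 252/0.85 gives 297, within the 300 planned.

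**2. Composite response, standard of care.** Inputs: vaccination 0.45; Table 1 blood pressure 74/93/89% and HbA1c 57/56/71% for clinics 1/2/3. Independence is an assumption.

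- Clinic 1: 0.45 × 0.74 × 0.57 = 0.190
- Clinic 2: 0.45 × 0.93 × 0.56 = 0.234
- Clinic 3: 0.45 × 0.89 × 0.71 = 0.284

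Re-randomised: 81%, 77%, 72%. Already vaccinated among them, (0.45 − r)/(1 − r): 32%, 28%, 23%.

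Without independence, the composite rate lies between max(0, sum of the three rates − 2) and the smallest of the three. That is 0 to 0.45 in clinics 1 and 2, and 0.05 to 0.45 in clinic 3. Nonresponse then ranges from 55% to 100%, and the vaccinated share of nonresponders from 0% to 45%.

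**3. Effect on a stage-2 vaccine contrast in the standard-of-care arm.** Assumptions: 126 participants (half of 252), an equal split, 0.45 v 0.70 among those not yet vaccinated, and those already vaccinated counted as successes in both groups. With f the vaccinated share, the difference is (1 − f) × 0.25.

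| Rule | Per group | f | Difference | Power |
|---|---|---|---|---|
| Vaccination only (r = 0.45) | 126 × 0.55/2 = 34.7 | 0 | 0.25 | 56% |
| Composite, r = 0.28 | 126 × 0.72/2 = 45.4 | 0.236 | 0.19 | 49% |
| Composite, r = 0.19 | 126 × 0.81/2 = 51.0 | 0.321 | 0.17 | 47% |

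The loss is about 7 to 9 points. The number of unvaccinated people per group is 34.7 in every row.

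**4. mHealth arm, illustration only.** The article gives no stage-1 vaccination rate here. At an assumed 70%, the same steps give 71%, 64% and 56% re-randomised, of whom 57%, 53% and 46% are vaccinated. For r = 0.44 and 0.30 the difference is 0.13 and 0.11, and power is 27% and 25%, against 34% under a vaccination-only rule.

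**The case against.** Several stronger readings are tempting, and the article does not support them.

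- **The rule defeats the targeting.** People with overdue services are intended recipients of care coordination. The Background says eligibility is widened to reduce outstanding services, Table 2 gives that as the added focus, and the Abstract lists service engagement among the primary outcomes. A two-part trigger follows from a two-part aim. This stands: the targeting is only weakened, and only for vaccination. The Abstract and Power calculations do disagree on whether services are primary, which adds to the need to reconcile.
- **Most participants are escalated because of the composite.** At 0.45 vaccinated, 55% of the standard-of-care arm are nonresponders on vaccination alone. In the mHealth arm, one stage-2 option is to stay on mHealth.
- **A service falling due late in stage 1 creates a nonresponder.** The article fixes neither an assessment date nor a baseline anchor. A condensed article may leave that to the full protocol, so no finding rests on it.
- **The sample size is too small.** Step 1 shows otherwise. Under the same inferred formula, the composite rates need fewer than 252.
- **Vaccinated nonresponders carry no information.** Table 4 ties up-to-date status to current guidance, boosters included, and the goal is a sustained rate. Status can lapse during stage 2.

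It is also fair that the article does not name a conditional stage-2 contrast as its powered comparison, and that means for the embedded strategies include vaccinated people under either rule. The Table 1 rates are clinic-wide and count screening at any time. Not everyone is due each service, while other listed services would lower the composite, so the proxy could err either way.

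None of this removes the mismatch between the two meanings of response, or the mixed stage-2 groups.

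**Conclusion.** The point holds in a limited form. The design and power sections use different definitions of response, and a participant can satisfy the power section's vaccine and service outcomes yet be re-randomised as a nonresponder. That follows from the text alone.

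The size is approximate. With two Table 1 services as proxies and independence assumed, about a quarter to a third of re-randomised standard-of-care participants would already be vaccinated, and the data allow anything from 0% to 45%. The resulting loss on a stage-2 vaccine contrast is modest, and that contrast has only 56% power even under a vaccination-only trigger. The power figures further assume that vaccinated participants stay up to date and that the full 0.70 v 0.45 difference applies among the unvaccinated. That 0.45 serves as the comparator's success rate is inferred from the numerical match to 252.

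This is worth correcting because the remedy is cheap. It is not a ground for enlarging the trial.

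**What to change.** 1. Reconcile the response definition in Methods, Design with the outcome definitions in Power calculations, and settle the status of preventive services between that section and the Abstract. Which definition should govern is for the investigators.
2. In Power calculations, say that 0.45 is the comparator's vaccination success rate, if that is what was used. State separately an assumed composite response rate with a range.
3. Stratify the second randomisation by COVID-19 vaccination status at re-randomisation (vaccination outstanding v services only), and adjust the stage-2 vaccine-uptake comparison for it.
4. Report the comparison restricted to those with vaccination outstanding as a supporting analysis only, because up-to-date status can lapse.

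The cost is one extra stratification factor at re-randomisation. The trigger already requires vaccination status to be known at that point, so no new data are needed.
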